**A. State of the art and objectives:**

**The objectives of the proposal: The aim of this study is to develop efficient cellular vaccine protecting from the diabetes type 1**

**Diabetes – basic epidemiology facts**

Morbidity of diabetes type 1 is getting higher each year in the majority of the developed countries. According to the International Diabetes Federation there were 193 mln of patients in 2003 and this number had increased to 246mln in 2007. Estimated number of diabetic patients in 2030 will be 366mln – around 5% of the human population all around the world will suffer from diabetes. Immune-mediated diabetes type 1 (DM1) consists of around 10-15% of all cases and the increase in this type of the disease is especially dramatic as DM1 affects mainly children and young adults. DM1 is diagnosed in 15/100 000 children in the US. In Finland, where the morbidity is the highest in the world, it is as much as 35/100 000. But DM1 is not only a Finland’s problem as the whole Eastern Europe note systematic increase in the ratio of new onset DM1. With all the development implemented in our side of Europe after communism fall, we have implemented also a burden of all risk factors of autoimmune diseases characteristic for the developed countries of the West. DM1 is a rising problem in Eastern Europe. For example, it is estimated that the morbidity in Poland is around 7/100 000 but in the most affected areas (Pomorskie and Lodz Regions) it is as high as 9.2/100 000, which means that the number of new onset DM1 doubled within 10 years only! (Bodalski J 2000)

**Diabetes as autoimmune disease**

It has been known from 80s’ of the XX century that DM1is an autoimmune disease. First, it has been found that the onset of the disease correlates with so-called insulitis, which is an inflammation in the pancreatic tissue with the presence of activated, self-reactive lymphocytes that infiltrate the pancreatic islets and destroy the insulin-producing beta cells (Gepts W 1981; Eisenbarth GS 1986). Then, it has been confirmed in animal models that the transfer of autoimmune anti-islet T cells from diabetic animals induced insulitis and diabetes in previously healthy animals (Bendelac A 1987). Although there is a long-lasting common agreement that such diabetogenic autoimmune T cells exist also in humans, their presence have been confirmed with tetramer technology only recently (Velthuis JH 2010).

Renewed interest on immunity in DM1 started with the discovery of highly suppressive T regulatory cells (Sakaguchi S 1995) which important role in the pathogenesis of this disease has been confirmed (Salomon B 2000). It has been found in several animal models that CD4+CD25+ T regulatory cells (Tregs) can stop destruction of pancreatic islets and protect from the development of autoimmune DM1 (You S; Green EA 2003). This finding was more difficult to confirm in humans, where the results were ambiguous. Some studies have revealed low level of Tregs in the peripheral blood of DM1 patients (Yang Z 2007), while others did not (Zavattari P 2004; Putnam AL 2005). A proof of principle came from the discovery of IPEX syndrome – recently described inherited disorder related to *Foxp3* gene in which patients do not have functional Tregs (Bennett CL 2001). Immanent features of IPEX (the immune dysregulation, polyendocrinopathy, enteropathy, X-linked) are dysregulation, related to the lack of Tregs, and diabetes, as a one of the endocrinopathies found in the syndrome due to Tregs deficiency. One may assume that similar dysregulation occurs in DM1. In this case, it does not only derives from a number deficiency of Tregs but it is also a result of functional impairment of this subset in DM1 patients (Brusko TM 2005; Lindley S 2005). Indeed, we and others found that in diabetes the proportion of fully functional CD62L+Tregs is decreased at the expense of so-called effector CD62L- Tregs with limited suppressive activity (Ryba M 2009). Hence, it is important to closely follow the phenotype of Tregs in DM1.

**Current immune-based therapies in diabetes**

The knowledge on autoimmune background of DM1 has been used in attempts to diagnose the disease and also to cure it. After few decades of discoveries we can precisely diagnose the patients assessing autoantibodies in their blood, like anti-GAD65, anti-insulin, anti-islets, anti-insulinoma-associated tyrosine phosphatase (IA-2), anti-fogrine and, anti-Zn transporter antibodies. This way we can even catch those in a prediabetic phase, before the clinical onset. Moreover, we can even select those at risk of the development of DM1 using HLA-typing (Rich R.R. 2008).

Such a sophisticated diagnostics can move the treatment of DM1 beyond an ordinary replacement of insulin which is a routine currently. The ultimate goal of the diagnostic process is the selection of a group of patients in which the pancreatic islets are still alive in a relatively high mass. Such patients can then receive treatment to save remaining islets and stop the clinical manifestation of DM1. Currently, there are two main streams of such treatment: with the administration of anti-CD3 antibodies and the manoeuvres encouraging immune tolerance to islets.

The idea of anti-CD3 administration was strictly related to autoreactive anti-islet T cells which destroy insulin-producing islets (Chatenoud L 1989). The antibodies were supposed to kill/deplete or inhibit unwanted effector T cells. In addition, it was found that the therapy enhanced beneficial regulatory T cell functions, thus promoting immune tolerance. Our centre takes a part in phase III trial with this drug. [after protocol: unfortunately, disappointing results of phase III trials and majority of the trials with different anti-CD3 antibodies were suspended]

Induction of immune tolerance is another area of immune-based therapies in DM1. Antigen-specific therapies with intranasal or oral administration of insulin or other peptides supposed to induce tolerance to islets still consists a big proportion of these interventions. In the majority of pre- and clinical studies, in which this strategy proved successful, the tolerance was dependent on Tregs (Staeva-Vieira T 2007). Hence, there are suggestions that simply cellular therapy with Tregs should be effective to stop DM1 (Brusko TM 2008).

**Idea of the current study: T regulatory cells vaccine for diabetes**

Recent development in biotechnology allowed for separation and expansion of Tregs. In our laboratory these cells are examined from the end of XX century and we were able to test all available methods of their separation and expansion (Trzonkowski P 2009b). The attempts to settle this research in the clinical context started in our laboratory in 2004 (Trzonkowski P 2004). In 2009 we achieved first clinical success with in vivo application of these cells [trial registered as NKEBN 458/2007- last amendment]. We achieved a significant reduction in drug doses administered and relieve of clinical symptoms in a group patients with chronic graft versus host disease with the longest remission lasting over two years (Trzonkowski P 2009a). The number of patients recruited to this trial is now eight patients as we are allowed to treat with expanded Tregs only those patients who do not respond to other therapies. Nevertheless, even with so small group in the follow up, we can state that all the patients tolerate well the administration of Tregs and nobody experienced side effects of the therapy.

Alive lymphocytes can be separated either with immunomagnetic kits or using FACS sorters. For several reasons the latter technique seems to be more useful in the work with Tregs in the human setting. Only a small proportion of CD4+ T cells with the highest expression of CD25 receptor and without CD127 receptor appears to have regulatory properties in humans. Purity of the preparation can be additionally improved with some other manoeuvres possible only with FACS sorters, such as doublet exclusion and multicolour phenotyping. With more than twenty different receptors checked in our laboratory, CD127-CD25highCD4+CD3+Lin-doublet- phenotype appeared to be optimal for clinical applications, notably for expansion under GMP conditions (Trzonkowski P 2009b).

When sorted, Tregs need to be expanded in order to be transferred to the patient. First of all, it requires certified GMP laboratory and the expansion procedure itself needs to be certified as well. It means that each and every element of the procedure including equipment and consumables needs to be checked and approved. At the same time, cultures of Tregs ex vivo are fragile and very easy decrease suppressive abilities. With all the efforts we were able to achieve stable cultures with good suppressive potential and now we are able to prepare preparation of Tregs approved according to the GMP requirements for patients. These requirements were already implemented in our university and the University of Chicago who cooperates with us (Marek N 2010). The quality of Tregs preparation easily decreases, mainly due to the time outside the body. Importantly, we found that both GMP conditions and reduction in the time of expansion are crucial for the success (Marek N 2010). Thorough analysis of the cultures of Tregs during expansion allowed us to optimize the procedure, so the suppressive abilities of these cells can be preserved throughout the whole expansion and patients can receive the product with more than 90% activity measured with FoxP3 expression. Importantly, in the two recently presented trials (ASH 2010) in which patients were treated with expanded Tregs the purity of the final product administered was around 60% and in some cases as low as 20% - close to the percentage of FoxP3 expression in total CD4 T cells [trials are now published: Brunstein CG 2011; Di Ianni M 2011].

**B. Procedures**

**All procedures are concordant with ‘the Medical Experiment requirements’ chapter of the Medical Doctor Act (Parliament of the Republic of Poland 1999 with amendments)**

1. **Recruitment**

The recruitment will be performed in the outpatient clinic of the the Department of Pediatrics, Hematology and Oncology Medical University of Gdańsk. Patients and parents will have a chance to discuss the study procedures and options with the recruiting named physician and time to read all necessary information related to the study (attached to this document as information for patients and parents).

1. **Blood drawing**

Recruited patients, after informed consent is signed by the parents, will be admitted to the Department of Pediatrics, Hematology and Oncology Medical University of Gdańsk. Blood will be drawn in the clinic by certified nurse according to the standard operating procedure of the ward for handling of blood samples. The only exception is the need of anastesiologist assistance during the procedure.

The volume of blood drawn will be calculated according to the following algorithm: Maximal volume of blood to be drawn is equal to 1% of the body weight but no more than 250ml [e.g. child weighting 20kg – 200ml of blood is allowed, child weighting 40kg – 250ml of blood is allowed ]. Then it will be separated in the blood bank to buffy coat and plasma and transferred to GMP laboratory [details of the transfer described in standard operating procedures for blood transport of the blood bank] for further processing.

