4. The proportion of subjects with ≥15% reduction of DDI/kg b.w. from baseline at 2 years after the administration of Tregs. The day of Tregs infusion is designated Day 0.
5. The proportion of subjects with ≥2% reduction of HbA1c from baseline at 120days after the administration of Tregs. The day of Tregs infusion is designated Day 0.
6. The proportion of subjects with HbAlc ≤6.5% at 120days after the administration of Tregs. The day of Tregs infusion is designated Day 0.
7. The proportion of subjects with HbAlc ≤7.0% at 120days after the administration of Tregs. The day of Tregs infusion is designated Day 0.
8. The proportion of subjects with HbAlc ≤6.5% at Day 365. The day of Tregs infusion is designated Day 0.
9. The proportion of subjects with HbAlc ≤7.0% at Day 365. The day of Tregs infusion is designated Day 0.
10. The proportion of subjects with HbAlc ≤6.5% from Day 0 to two years after the administration of Tregs. The day of Tregs infusion is designated Day 0.
11. The proportion of subjects with HbAlc ≤7.0% from Day 0 to two years after the administration of Tregs. The day of Tregs infusion is designated Day 0.

Efficacy Endpoints:

At 120 ± 14 days following the adoptive transfer of Tregs:

- - - - - The proportion of subjects with DDI ≤ 0.5UI/kg b.w.
        - The proportion of insulin-independent subjects
        - C-peptide levels
        - HbAlc levels
        - Quality of life (QOL) measures
        - Functional tests results [can only be performed when indicated by medical conditions of the patients and NOT solely as an efficacy check as recommended by the Ethics Committee]

At 365 ± 14 days following the adoptive transfer of Tregs:

- - - - - The proportion of subjects with DDI ≤ 0.5UI/kg b.w.
        - The proportion of insulin-independent subjects
        - C-peptide levels
        - HbAlc levels
        - Quality of life (QOL) measures
        - Functional tests results [can only be performed when indicated by medical conditions of the patients and NOT solely as an efficacy check as recommended by the Ethics Committee]

At 2 years ± 14 days following the adoptive transfer of Tregs:

- - - - - The proportion of subjects with DDI ≤ 0.5UI/kg b.w.
        - The proportion of insulin-independent subjects
        - C-peptide levels
        - HbAlc levels
        - Quality of life (QOL) measures

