1. Patients fulfilling the inclusion criteria from 1 to 6 but
2. EXCLUDED from blood drawing due to inappropriate venous access.

Exclusion Criteria:

Patients who meet any of these criteria are not eligible for participation in the study:

1. No agreement for participation in the study and no inform consent singed
2. Other than autoimmune type 1 diabetes
3. Age below 5 and above 18 years at the time of recruitment
4. Carriage of HLA-DQB1*0602 allele
5. IgA deficiency or other genetic defect present
6. Body mass index (BMI) outside the range of 25-75 percentiles for a particular age.
7. Presence or history of active infection including hepatitis B, hepatitis C, HIV, syphilis or tuberculosis (TB). Subjects with laboratory evidence of active infection are excluded even in the absence of clinical evidence of active infection.
8. Invasive aspergillus, histoplasmosis, or coccidioidomycosis infection within one year prior to study enrollment.
9. Any history of malignancy
10. Baseline Hb below the lower limits of the reference range ; lymphopenia (<l,000/uL), neutropenia (<l,500/uL), or thrombocytopenia (platelets <100,000/uL).
11. Known hypercoagulative state.
12. Medical treatment requiring chronic use of drugs other than insulin
13. Treatment with any anti-diabetic medication other than insulin within 4 weeks of enrolment (special attention to exclude anti-CD3 treated patients).
14. Diabetic retinopathy.
15. Arterial hypertension.
16. Presence or history of macroalbuminuria (>300 mg/g creatinine).
17. For female subjects older than 15 years positive pregnancy test, unwillingness to use effective contraceptive measures for the duration of the study and 4 months after discontinuation, when appropriate. For male subjects: intent to procreate during the duration of the study or within 4 months after discontinuation or unwillingness to use effective measures of contraception when appropriate.
18. Excessive anxiety of the patient or parents related to the procedures.
19. Any medical condition that, in the opinion of the investigator, will interfere with safe participation in the trial.
20. For parents and children older than 15 years: known active alcohol or substance abuse.

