**3.2.2. Tregs expansion**

[figure not shown]
Figure B.3.2: Ex vivo expansion of Tregs

The flowchart outlines the procedure, starting from sorting of the Treg cells.

CD127lowCD25highCD4+CD3+ sorted Tregs will be cultured in 96-well U-bottom plates. Tregs (1 × 105 per well) will be cultured in a high dose of IL2 (1,000 IU/ml) and anti-CD3/CD28 beads in 1:1 ratio in autologous heat-inactivated serum. Importantly, all media and cytokines will keep GMP-grade certificate. The cells will be passaged every two days during the first week and every day during the second week with new medium supplemented with IL2. On day +7, the beads will be replaced with a fresh set (one bead per cell). The number of cells increases exponentially and the desired number of cells is usually achieved between 7th to 14 day of the culture. At the day +7 and at the end of the culture, the product is checked for quality as described below. The culture is stopped either when the desired number of cells is achieved or at the day +13 of the culture. Cells are washed out from expansion beads and IL2 and suspended in medium with 10% autologous serum for 24 hours. After this time certification is performed and the cells are suspended in 250ml of 0.9% NaCl and closed in thermostable container in order to be released. These conditions are also published in Cell Transplantation journal (Marek N 2010).

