**5. Follow up of the patients**

Patients will be examined at recruitment, the day of blood drawing for Tregs expansion, at the day of Tregs infusion and two weeks later, every two months for the first half a year, then every 3 months for the duration of the study (2 years). In each point of the study 15ml of venous peripheral blood will be taken: 8ml on EDTA for cellular analyses (flow), 5ml without anticoagulant for serum and 2 ml for DNA.

Control patients – after recruitment blood taken during routine visits only.

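### The blood harvest, done in the Treg arm only, is expected to lower HbA1c at Day 0 and +14 days for reasons other than glycaemia, and secondary endpoints 10 and 11 (possibly 5) take in those readings

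*Protocol*

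**What the plan says.** **Harvest.** Section B, Blood drawing, states the limit: "Maximal volume of blood to be drawn is equal to 1% of the body weight but no more than 250ml". Its worked examples are "child weighting 20kg – 200ml of blood is allowed, child weighting 40kg – 250ml of blood is allowed". On what happens next it says "Then it will be separated in the blood bank to buffy coat and plasma", with transfer to the GMP laboratory. Return of the red cells to the child is not mentioned.

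**Controls.** They meet inclusion criteria 1 to 6 but are "EXCLUDED from blood drawing due to inappropriate venous access". Section 5 adds: "Control patients – after recruitment blood taken during routine visits only".

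**Timing.** Section 3.2.2 says the target cell number is usually reached from day 7 of culture and sets a limit: "The culture is stopped either when the desired number of cells is achieved or at the day +13 of the culture". A further 24 hours in serum-supplemented medium precedes release.

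**Readings.** The follow-up visit schedule lists HbA1c at recruitment (R), blood drawing (A), day 0, +14 days, +2 months and every later visit.

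**Endpoints.** Secondary endpoint 10 is "The proportion of subjects with HbAlc ≤6.5% from Day 0 to two years after the administration of Tregs" and endpoint 11 is "The proportion of subjects with HbAlc ≤7.0% from Day 0 to two years after the administration of Tregs". Endpoint 5 counts an HbA1c reduction from baseline at 120 days without naming the baseline visit. Endpoints 6 to 9 use only the 120-day and Day 365 values.

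**The concern.** HbA1c depends on how long red cells have been exposed to glucose as well as on the glucose level. When a child loses red cells and replaces them, the circulating cells are younger on average and HbA1c falls although glucose has not changed. This is general physiology; the protocol does not state it. The protocol does foresee red-cell loss, since a haemoglobin fall of more than 2 g/dL from the draw is one of its safety items, but it does not carry this over to HbA1c.

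The harvest coincides with arm: Treg children undergo it and controls by definition do not. Two scheduled HbA1c readings follow it within about four weeks. An endpoint that uses them mixes a laboratory effect of the harvest with glycaemia. In endpoints 10 and 11 this would help Treg children pass the early readings. In endpoint 5, with Day 0 as baseline, it would hide part of the later fall. With 10 children per arm, one reclassified child moves an arm's proportion by 10 percentage points.

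**Working it through.** **1. Volumes.** Volume = min(10 ml/kg × weight, 250 ml). At 20 kg this is 200 ml; at 40 kg it is 400 ml capped to 250 ml. Both match the protocol's examples. The cap applies above 25 kg.

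**2. Share of blood volume.** f = volume / (b × weight). The documents give no b, so I assume 75 ml/kg (range 70 to 80).

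| Weight | Volume | f at 75 ml/kg | f at 80 to 70 ml/kg |
|---|---|---|---|
| up to 25 kg | 10 ml/kg | 13.3% | 12.5 to 14.3% |
| 40 kg | 250 ml | 8.3% | 7.8 to 8.9% |
| 60 kg | 250 ml | 5.6% | 5.2 to 6.0% |

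**3. Timing.** Taking culture to start on the day of the draw, Day 0 falls 7 + 1 = 8 to 13 + 1 = 14 days after it. The +14 day reading falls 22 to 28 days after it.

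**4. Model (every input assumed).** Red cells live 120 days with uniform ages, HbA1c is proportional to mean cell age, red cells are not returned, and the lost fraction f is restored linearly over T days, with T from 21 to 56. At t days after the draw the relative change in HbA1c is:

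- for t ≤ T: −f (t/T)(1 − t/120) / [(1 − f) + f t/T]
- for t > T, up to day 120, with the red-cell total then held constant: −f + f (t − T/2)/60

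Example with f = 0.133, t = 14, T = 21: −0.133 × 0.667 × 0.883 / (0.867 + 0.089) = −0.0785 / 0.956 = −8.2%. With T = 56 the result is −3.3%.

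**5. Results over T = 21 to 56 and the range of t.**

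| Loss | Day 0 (t = 8 to 14) | +14 d (t = 22 to 28) |
|---|---|---|
| 13.3% | −2.0% to −8.2% | −4.7% to −10.9% |
| 8.3% | −1.2% to −5.0% | −2.8% to −6.8% |
| 5.6% | −0.8% to −3.3% | −1.8% to −4.5% |

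The change is downward in every cell.

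**6. Sensitivity at 13.3% loss.** If new cells start at 30% of mean HbA1c rather than zero, the falls shrink to 2.3 to 5.7% at day 14 and 3.8 to 7.1% at day 28. A variant that also lets glucose before diagnosis be twice the later level, with T = 28 to 56, gives falls at a true 8% of 0.26 to 0.63 points at day 14 and 0.43 to 1.04 points at day 28. The last figure is 1.04/8 = 13%, somewhat beyond the table.

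**7. Later visits at 13.3% loss.** At +2 months (t about 69 to 75) the formula gives −4.2% to +1.0%. Near +4 months the answer depends on the assumed red-cell production after recovery: one rule gives a rise of 0.31 to 0.50 points at a true 8%, and another gives −3.7% to +5.4%. The sign is not settled.

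**8. Illustration of consequence.** Assume HbA1c at one reading has mean 7.5% and SD 1. A shift of −0.3 points (4% relative) raises the share at or below 7.0% from 31% to 42%, and the share at or below 6.5% from 16% to 24%. That is about one child in ten.

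**The case against.** The strongest objection is that the core is not in the document. The protocol links the draw to HbA1c nowhere; blood volume, cell life, glycation law and recovery time are all assumed, and the laboratory procedures that might say what becomes of the red cells are not shown. The children are within two months of diagnosis, so glucose is changing while the model holds it constant. This stands against any exact size. It does not overturn the direction at Day 0 and +14 days, which was downward in every scenario run, provided the red cells are not returned.

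Second, 13% is a maximum for children of 25 kg or less, and the age range is 5 to 18 years. This stands, and the table in the working shows smaller effects at higher weights.

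Third, a reader might infer that the HbA1c endpoints are biased between the arms in favour of Treg. The documents do not support that:

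- Controls receive no infusion and are sampled at routine visits, so they have no scheduled Day 0 or +14 day reading to set against the Treg values. This gap is visible in the text and is more basic than the red-cell effect.
- Endpoint 5 is touched only if Day 0 is its baseline, and there the shift runs against the Treg arm.
- Endpoints 6 to 9 do not use the two early readings.
- Endpoints 10 and 11 do not say that every visit must pass. If that is meant, an early shift matters only for a child who also passes all later visits.

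Fourth, naming a baseline is often left to an analysis plan, and these are secondary endpoints in a pilot of 10 + 10. That limits the severity. It does not alter the fact that the window of endpoints 10 and 11 is fixed in the protocol and opens inside the affected period.

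**Conclusion.** The point holds as a minor one. From the protocol alone: the harvest is confined to the Treg arm, it precedes Day 0 by about 8 to 14 days, HbA1c is scheduled at Day 0 and +14 days, and endpoints 10 and 11 begin at Day 0. By inference from general physiology, and on condition that red cells are not returned, HbA1c at those two readings is expected to be lower than glycaemia warrants. The rough size is 1 to 8% relative at Day 0 and 2 to 11% at +14 days, depending on weight and recovery time, and it rests wholly on the assumed model.

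The working does not support a definite sign at +2 or +4 months, a fixed threshold at which a child would be misclassified, or one overall direction of bias across the HbA1c endpoints. The primary endpoints rest on adverse effects, insulin dose and C-peptide and are unaffected.

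**What to change.** Change the wording of the endpoint definitions:

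1. Define the HbA1c baseline in both arms as the recruitment (R) value, which precedes the harvest. This also settles endpoint 5.
2. Base endpoints 10 and 11 on visits from +2 months onward, matched to the control visits by time since recruitment.
3. Report the Day 0 and +14 day HbA1c values descriptively only.
4. State that a residual harvest effect at +2 to +4 months cannot be excluded. Starting at +2 months drops the two readings with a clear expected direction; it does not guarantee that later ones are free of the effect.

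Cost: two early readings per Treg child leave two secondary endpoints. No visit or sample is added in the Treg arm. Matching depends on when the control children's routine visits fall, which the protocol does not fix.
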